#### Pedometer Group

Participants will be provided with a digital pedometer (Digi-walker CW-700/701, YAMAX, San Antonio, TX). The pedometer records total number of steps (steps), activity time (hour/minute), distance walked (mile), and calories burned (kcal). The device stores this information every day and up to the previous 7 days. Weekly totals for steps, activity time, distance walked, and calories burned are stored for the current and previous week. The pedometer also displays a clock and an informative graph that estimates the number of calories burned based on the number of steps [51]. Participants will be instructed to log their daily steps, activity time, and distance walked measured by the pedometer in an activity diary.

#### Electronic Activity Monitors Group

All participants will be given an EAM (UP24 by Jawbone, San Francisco, CA) and the corresponding UP app on their smart device. UP24 by Jawbone is widely used and is one of the top selling EAMs [52]. Furthermore, UP24 implements the most BCTs compared to other available EAMs and provides vital techniques that are missing in the counseling. In total, Jawbone UP24 provided 27 BCTs in 2014, but with continual software updates, this number is likely higher [38]. Some examples include goal setting on behavior and on a health outcome, self-monitoring of behavior, emotional social support, providing instructions, providing information on consequences, social comparison, prompts, and focus on past success [38]. For these reasons, UP24 was selected for the intervention.

The UP app provides information related to PA, diet, weight, sleep, and socialization. Participants will not be counseled on improving sleep or diet, but they are additive features of the app. The home screen of the app provides immediate feedback to the user on their activity for the day. On the home screen, the wearer also has access to their activity feed, which displays all their activities and their teammates’ activities. All activities in the app are stored forever so the user can review all past activity. In addition, the app allows the user to set goals, record activity, and review activity trends. The user can also set reminders for activity and learn more information about their health from the Smart Coach tailoring messaging feature [53]. The specific features throughout the app are described in Multimedia Appendix 2 (see Multimedia Appendix 2).

All participants will be given a deidentified account with an anonymous name and icon to use in the app. We have chosen to use board game pieces names and icon pictures (eg, Battleship, Cat, Hotel) based upon suggestions from previous participants and enjoyment of this system in our pilot studies. Participants will be required to add other participants as their “teammate” in order to utilize the socializing features within the app. Only PA information will be required to be visible by their teammates. Participants will be able to customize their account if they wish to share any other behaviors with their teammates. Participants that do not consent to have their deidentified information shared with other participants will be ineligible and dropped from the intervention. In order to view the participant’s activity, the participants will also add the research account as a teammate. The researchers will not socialize or interact with the participants through the app; it will be for surveillance purposes only. Participants will be given a trouble-shooting guide to help with any issues with the app. The researcher will also review and resolve any technical issues reported during the “Arrange” phone call.

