### Recruitment and Screening Procedures

Participants will be recruited from two clinics affiliated with a large university-based health care system. Recruitment started in October 2015 and will continue until all participants are enrolled. Prospective participants will be recruited from flier postings in waiting rooms and in patient rooms, direct solicitation from a recruitment table in the lobby, and through recruitment letters mailed to their home.

Patient eligibility will be determined by using a screening script. Screenings will be completed in person at the recruitment table or over the phone. Once patients are deemed eligible, the researchers will obtain informed consent. This will be done promptly after screening for eligibility at the recruitment table for patients screened in person. For patients screened over the phone, a researcher will arrange a meeting with the patient at their primary care clinic to obtain informed consent.

After obtaining informed consent, an assessment visit will be scheduled. Reminders about the orientation meeting will be sent via email monthly (for those recruited prior to the data collection start date of January 1, 2016) and one week prior to the scheduled meeting. In addition, participants will receive a phone call reminder the day before the meeting. Enrollment into the intervention is postponed until after January 1, 2016 to minimize seasonal variations in PA [49].

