#### Grouping the Participants

All participants will be given an activity monitor to encourage self-regulation of PA. After counseling, participants will be randomized to one of the two groups: pedometer or EAM group. A random number generator available on the Internet will be used to randomly allocate group assignment [50]. Assignment into the EAM group will be selected randomly by the generator using the following settings: 1 set, 5 unique numbers, numbers range from 1 to 10, and sorted lowest to highest. This process will be repeated for 3 more sets of numbers ranging from 11-20, 21-30, and 31-40. Each number represents a participant identification number selected to be in the EAM group. Group assignment will be written on a piece of paper wrapped in foil and carbon paper and concealed inside an envelope prior to group allocation. A blinded researcher will prepare all of the envelopes. After group allocation, participants will be given all intervention materials and detailed instructions on all intervention components. For participants in the EAM group, the researcher will also test the monitor and the participant’s smart device to ensure they are working properly. Due to the nature of the intervention, the participants and the accessor will not be blinded to group assignment after randomization.

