### Statistical Analyses

The Statistical Package for the Social Sciences (version 20) will be used to perform all quantitative statistical analyses. Analyses will be completed in two ways: first using the intent-to-treat principle (primary analysis) and then only with adherers to the intervention (secondary analysis for the purpose of informing further intervention refinement). The alpha-level to determine significance is set at .05. The specific statistical procedures, by research aim, are described below.

### Aim 1

Feasibility findings will be primarily descriptive and used as a metric for improvement when compared to similar studies. For example, days worn will be compared to other EAM studies, whereas attrition will be compared to other primary care-based studies. Rather than determine dichotomous feasibility or not, we will use relative feasibility to determine areas of focus for intervention refinement; which is addressed in the follow-up questionnaire and in focus groups. Comparisons of adherence between EAM and pedometer groups is covered under Aim 2 below and the procedures for analyzing focus groups will be identical to procedures outlined in Aim 3 below.

We hypothesize that the intervention will be feasible among several improvement metrics including ≥ 70% days the monitor is worn [37], < 20% attrition [73], and < 8 moderate or higher adverse events (< 20% of participants reporting an adverse event) [74-76]. Hypotheses based on other feasibility metrics include a low frequency of technical difficulties and a high frequency of app usage. Additionally, the intervention will be accepted among participants based on self-report questionnaires and focus group responses. We also hypothesize that the EAM group will show higher feasibility and acceptability compared to the pedometer group.

### Aim 2

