### Data Management

Participants will be thoroughly informed of study procedures and give informed consent prior to any data collection. All data and participant information will be kept in a locked file cabinet or stored as a deidentified file on a secured computer network. Data and participant information will be transported from the clinics to the office in a passcode protected folder or on an encrypted flash drive. Data will be linked with an identification number and will be stored separately from all personal information. Only authorized members of the research team will have access to data. Due to the small sample size, a data monitoring committee will not be utilized. Instead, the Principal Investigator will conduct data safety monitoring weekly.

Participants in the EAM group will be given deidentifiable accounts to be used by the UP app. The accounts will not provide names, images, or personal information of the participants. UP app accounts made by stakeholders, as part of their involvement in the focus groups, will not be deidentified and will include any personal information the individual discloses in the app (ie, name, images). Accounts will only be viewable by other study participants and the research team.

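### The rule that drops people who refuse to share app data can act only in the EAM arm and has no fixed timing, so it permits one-arm removal after randomisation

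*Protocol article*

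**What the plan says.** All places are in the protocol article.

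- **The rule.** Electronic Activity Monitors Group: "Participants that do not consent to have their deidentified information shared with other participants will be ineligible and dropped from the intervention".
- **Who has something to share.** Data Management: "Participants in the EAM group will be given deidentifiable accounts to be used by the UP app". The Pedometer Group section describes a step counter and a paper diary, with no account and no teammates.
- **Order of events.** Grouping the Participants: "After counseling, participants will be randomized to one of the two groups: pedometer or EAM group". It continues: "After group allocation, participants will be given all intervention materials and detailed instructions on all intervention components". From that point "the participants and the accessor will not be blinded to group assignment after randomization".
- **Consent.** Recruitment and Screening Procedures: "Once patients are deemed eligible, the researchers will obtain informed consent". This precedes the assessment visit and therefore randomisation.
- **Eligibility.** The list under Protocol includes failure to consent as a general exclusion. Neither that list nor the screening section names agreement to share app data.
- **Analysis.** Under Statistical Analyses the work is done in two ways, "first using the intent-to-treat principle (primary analysis", and then in adherers only. Aim 1 sets an attrition benchmark of under 20%. Aim 2 compares retention and days of monitor wear between the arms.

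**The concern.** A criterion that makes people ineligible should be settled before randomisation and apply to both arms alike. Followed where it stands, this one does neither. A person randomised to the EAM who balks at sharing with teammates could be declared ineligible, while an identical person randomised to the pedometer would never be asked. The decision would be taken when participant and assessor both know the allocation.

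The trial's main purpose, feasibility and acceptability, is the most exposed. The article hypothesises that the EAM arm will do better on both, and interaction with other app users is itself a feasibility measure. Refusing the social feature is informative about acceptability. If it is filed as ineligibility, that information leaves the results, and it leaves from one arm only.

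**Working it through.** No stated figure decides this point, and the sample-size statement about 1000 steps plays no part in it. The check sets the passages side by side and then sizes the consequence under stated assumptions.

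**1. Which arm can the rule act in?** Only EAM participants have accounts (Data Management), so only they have app data to share with teammates. As described, the rule is one-armed.

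**2. When does it act?** Two readings fit the text.
- *Before randomisation:* consent is taken at enrollment, ineligible is enrollment language, and the time-frame table shows an eligibility screen at both enrollment and allocation.
- *After randomisation:* the sentence belongs to the description of account and teammate set-up, materials are handed out after allocation, and being dropped implies that the person was already in.

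The article does not choose between them.

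**3. What happens to a dropped person?** The text says dropped from the intervention. It does not say whether the person stays in follow-up, in the intent-to-treat set or in the attrition count.

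**4. The plan's own counts.** Randomisation draws 5 EAM numbers in each of 4 sets of 10: 4 × 5 = 20 EAM and 40 − 20 = 20 pedometer. Under Aim 1, 20% of 40 is 8 participants, which agrees with the article's pairing of fewer than 8 adverse events with under 20%.

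**5. Size if refusers were removed from the analysis.** Assume k of the 20 EAM participants are removed, and that those kept exceed those removed by d SD on the outcome. The full-arm mean is [(20 − k) × kept + k × removed]/20, so

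bias = kept − full-arm mean = (k/20) × d.

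For an unadjusted two-sample normal test with no true effect, SE = √(1/(20 − k) + 1/20), and

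P(reject) = 1 − Φ(1.96 − bias/SE) + Φ(−1.96 − bias/SE).

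Example, k = 2 and d = 1.0: bias = 0.10, SE = √(1/18 + 1/20) = 0.325, bias/SE = 0.308, P = 0.061.

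| k removed | Share of EAM arm | Bias, d = 0.5 | Bias, d = 1.0 | Type I error, d = 0.5 | Type I error, d = 1.0 |
|---|---|---|---|---|---|
| 1 | 5% | 0.025 SD | 0.05 SD | 0.051 | 0.053 |
| 2 | 10% | 0.05 SD | 0.10 SD | 0.053 | 0.061 |
| 4 | 20% | 0.10 SD | 0.20 SD | 0.060 | 0.092 |

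With k = 0, or with refusers followed and analysed as randomised, the bias from this rule is zero and the type I error stays at 0.05.

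**6. Effect on the retention comparison.** Suppose 2 EAM participants refuse and 2 others leave. Counted as randomised, EAM attrition is 4/20 = 20%. With refusers classed as ineligible it is 2/18 = 11.1%. The pedometer denominator stays at 20 in both cases.

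**The case against.** The strongest reply is that the harmful reading is inferred. Timing rests on where the sentence sits. General consent comes before randomisation, lack of consent is an exclusion for everyone, and the full protocol and consent form, which may settle the matter, are not shown. This stands in part: it rules out saying that the trial will exclude randomised people. It does not remove the defect, because the article states a rule and the rule's wording supports both readings.

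Four stronger inferences are tempting, and the documents do not support them.

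- **That the rule breaks intent-to-treat.** Being dropped from the intervention is not being dropped from the analysis. Intent-to-treat is named as primary, and nothing says that refusers leave follow-up. The rule permits a breach; it does not state one.
- **That the device check is a second one-arm exclusion.** The article says "For participants in the EAM group, the researcher will also test the monitor" and the participant's own device, but attaches no removal to a failed test. Access to a compatible device is already required of everyone.
- **That relabelling turns a failed attrition benchmark into a pass.** The under-20% figure is not set per arm. With 2 refusers and 2 other leavers, trial-level attrition is 4/40 = 10% or 2/38 = 5.3%, and both are below it. Aim 1 also disclaims a yes-or-no feasibility decision.
- **That the bias must favour the EAM.** No passage shows that people who decline sharing are less active or less adherent. The direction and size of d are assumptions.

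It is also fair that Aim 2 calls the between-group outcome comparisons exploratory. That lowers the stakes for physical activity and cardiovascular risk. It does not lower them for feasibility and acceptability, which are the primary purpose.

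**Conclusion.** The point holds as an ambiguity with consequences. The protocol article states a removal rule that can act only in the EAM arm, places it among post-allocation procedures, and leaves it off the eligibility list. It does not say when agreement to share is obtained or how a randomised refuser is counted. If refusal surfaces after allocation and refusers leave follow-up or the denominators, the result is differential, unblinded, post-randomisation exclusion, which conflicts with the intent-to-treat primary analysis. If everyone agrees before randomisation, there is no bias from this rule.

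Severity is moderate. For 1 to 4 removals (assumed) and d of 0.5 to 1.0 SD (assumed), the shift in the group difference is 0.025 to 0.20 SD and the type I error is 0.051 to 0.092. These values come from an unadjusted test, not the planned analysis of covariance. The more direct risk is to the between-arm retention comparison and the acceptability results, where a few people out of 20 change the figure visibly.

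**What to change.** 1. Under Protocol, list agreement to share deidentified activity data with other participants as an eligibility item for all participants, whichever arm they may enter. Have it confirmed before the envelope is opened, including for those already enrolled.
2. Under Statistical Analyses, state that any randomised participant who later refuses sharing is followed to the 12-week assessment, analysed as randomised, and counted in the retention, adherence and acceptability results.
3. Reword the sentence in the EAM section to match. Whether such a person goes on using the device is for the investigators to specify; the analysis rule applies either way.

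**Cost.** The text change is a few sentences, and the planned 20 versus 20 is unaffected. A few refusers will be lost before randomisation, which slightly narrows the population. Eight participants were enrolled by December 3, 2015. If their consent did not cover sharing, a small amendment and a re-check of those people may be needed. The intervention was due to start only after January 1, 2016, so on the article's own dates this could be done before the first allocation.

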### Assessment Procedures

The primary purpose of this study is to investigate the feasibility and acceptability of a low-intensity intervention that combines 5 A’s counseling and an EAM system. We will also compare the effects of these high-tech activity monitors to low-tech ones (pedometers) on PA and other cardiovascular risk indicators (Framingham risk calculator, fitness). The study includes two assessments conducted at baseline and 12 weeks. Upon initial recruitment at the clinic, participants will provide informed consent and schedule their first assessment visit. Approximately 7 days before their initial assessment, participants will be given a baseline questionnaire and a research-grade activity monitor (discussed below) to wear for a 7 day baseline period. Participants will return to their primary care facility to complete the assessment. At 11 weeks, participants will be given a follow-up questionnaire and the research-grade monitor to wear for 7 days. At 12 weeks, participants will return to their clinic to complete assessments identical to baseline. As reimbursement for taking part in this study, all participants will receive a US $25 gift card at the end of the 12 week assessment, and at that time participants also forfeit their EAM or pedometer device.

The primary outcomes of interest are feasibility and acceptability. Feasibility will be operationalized in several ways. Number of days logged for activity, interactions with other users in the mobile app, and additional use of the app will be abstracted using procedures we have previously pilot tested successfully. Acceptability will be measured using self-report (modeled on items previously developed) [54], responses, and focus groups conducted after completion of the intervention. The primary physiological variables of interest include cardiovascular risk indicators and PA. Secondary outcome variables are anthropometrics, body composition, blood pressure, exercise motivation, health status and quality of life, physical function, psychological feelings, resting pulse, and self-regulation. All physiological study variables are listed in Table 4.

**Table 4 table4:** Study variables.

Variable		Measure	Subscales	Alpha statistics
**Primary variables**				
	CVD risk	Framingham nonlaboratory risk score calculator	Age: yrs; body mass index: *kg*/m^2^; systolic blood pressure: mmHg	
		Six minute walk test	Distance walked in 6 minutes: ft	
	PA	Sensewear armband (BodyMedia, Pittsburgh, PA)	Minutes of METs ≥ 3 (7 days of measurement); steps per day	
**Secondary variables**				
	Anthropometrics	Stadiometer (Seca Corp, Hamburg, Germany); scale (Tanita, Arlington Heights, IL)	Height (baseline only): cm; weight: kg; body mass index: *kg*/m^2^	
	Body composition	Tape measure (Singer, China)	Waist circumference: cm; hip circumference: cm; waist to hip ratio	
	Blood pressure	Sphygmomanometer (Omron BP742N, Lake Forest, IL)	Systolic blood pressure: mmHg; diastolic blood pressure: mmHg	
	Demographics	Self-report	Age: yrs; sex; race/ethnicity; education	
	Exercise motivation	Behavioral Regulation in Exercise Questionnaire-2	Intrinsic, identified, introjected, extrinsic, amotivation	.73-.86
	Health status and quality of life	36-Item Short Form Health Survey	Physical functioning, social functioning, physical role limitations, emotional role limitations, mental health, energy/vitality, pain	.76-.90
	Physical function	Short physical performance battery	Repeated chair stands, balance, semitandem stand, side-by-side stand, tandem stand, 8 feet walk	
		PROMIS SF v1.2-Physical function 8b	Upper extremities, lower extremities, central regions	
	Psychological feelings	Psychological Need Satisfaction in Exercise Scale	Perceived competence, perceived autonomy, perceived relatedness	>.90
	Resting pulse	Sphygmomanometer (Omron BP791T, Lake Forest, IL)	Heart rate: bpm	
	Self-regulation	Rovinak et al scale [55]	Exercise goals, exercise plans	.87-.89

### Cardiovascular Risk

CVD risk is determined by measuring 10 year risk of cardiac event from the Framingham nonlaboratory equation [56] and from fitness measured by a six minute walk test [57]. The six minute walk test is an additive assessment of CVD risk because cardiorespiratory fitness is the result of chronic PA and is more strongly related to clinical outcomes [58]. The Framingham equation has been used to estimate CVD risk in previous studies [31,59]. It requires a combination of self-report and objective measures [56,60]. Self-report measures include sex, age, treatment of hypertension, smoking status, and diagnosis of diabetes. Objective measures included blood pressure and body mass index [56,60].

The six minute walk test requires participants to walk a 100 feet course continuously for 6 minutes. It has been validated in older adults to measure physical endurance (0.71<r<0.82) [57]. Percentile norms on the test have been established for active older adults [61].

### Physical Activity

PA will be measured with a SenseWear Armband. The armband is worn on the upper arm for 7 days. SenseWear quantifies PA by measuring expended kcals/week, minutes of activity a day, and steps per day. There is a mean error < 5% in measuring total minutes of PA with the SenseWear armband [62]. To properly program the armband, age, gender, and body mass index (BMI) will be collected at enrollment. These variables will be formally measured at a study allocation, described below.

